## Abstract

**Abstract:**

**Introduction:**

Cardiovascular disease is one of the most common health issues facing the older population, and the number of older adults undergoing cardiac surgery is expected to increase. Postoperative neurocognitive impairment is a frequent and often unrecognised complication that can adversely affect a patient’s recovery, quality of life and daily activities, as well as impact the lives of their family members. Patients may express cognitive difficulties as a feeling of ‘not being the same since the operation’. This study aims to investigate the factors that influence neurocognitive function and patient-reported cognitive symptoms among patients aged 65 and older following cardiac surgery, and explore the impact on the overall postoperative recovery. Additionally, the study aims to describe the perspectives of close relatives on the recovery process.

**Methods and analysis:**

A longitudinal observational study with a mixed-methods approach will be conducted in two thoracic surgical departments in Sweden. A total of 220 patients and 1 close relative for each patient will participate. Neurocognitive function will be assessed preoperatively and at 1, 3 and 6 months postoperatively using a digitalised neurocognitive test battery. We will also evaluate postoperative patient-reported cognitive symptoms and signs, delirium, frailty, health-related quality of life, depression, perceived self-efficacy, fatigue and functional capacity. Each patient’s close relative will assess the observed cognitive function and report on caregiver burden. At the 6-month mark, a purposive sample of patients and their close relatives will be interviewed to explore their experiences of postoperative cognitive recovery.

**Ethics and dissemination:**

The study has been approved by the Swedish Ethical Review Authority (Reference number: 2024-03380-01) and will adhere to the Helsinki Declaration and its amendments. The results will be disseminated through peer-reviewed journals and scientific conferences, as well as presented in various popular science forums and patient organisations.

**Trial registration number:**

NCT06469515; Pre-results.

STRENGTHS AND LIMITATIONS OF THIS STUDYThis study employs a novel approach to assess neurocognitive function through a digital self-administered neurocognitive test battery.By employing a mixed-methods approach, the study provides a comprehensive, reliable and flexible analysis, contributing to a more complete and nuanced understanding of cognitive recovery following surgery, particularly from the patient’s own perspective.Incorporating the experiences and perspectives of close relatives will enhance our understanding of neurocognitive function and the process of returning to everyday life after cardiac surgery.However, the study has a high response burden, which increases the risk of participant dropouts and may impact the quality of the data collected.

## Introduction

 The global population of older adults is increasing rapidly, making this demographic group the fastest-growing worldwide. By 2070, it is projected that one in four people in Sweden will be 65 years or older,^1^ and similar trends can be observed globally.^2^ As cardiovascular disease is one of the most common health issues among older adults, it is anticipated that the number of older adults undergoing cardiac surgery will also rise.^3 4^ Older adults are more susceptible to postoperative complications, which are often medical rather than surgical in nature. They tend to experience longer hospital stays and higher rates of readmission compared with the general population.^5^ Additionally, many older adults face multimorbidity,^6^ and a significant number may be classified as frail,^7^ whether or not they have pre-existing cognitive impairments.^8^

Postoperative neurocognitive impairment is a frequent yet often unrecognised complication following cardiac surgery, which can affect the patient’s recovery, quality of life and daily functioning, as well as impact their close relatives.^9^ Perioperative neurocognitive disorder, previously known as postoperative cognitive dysfunction, is an overarching term used to describe cognitive impairment that occurs post-surgery, reflecting a decline in neurocognitive performance from the preoperative baseline.^10^ This includes postoperative delirium (POD), characterised by a sudden decline in attention and cognitive function occurring within 7 days after surgery, delayed neurocognitive recovery (dNCR), which refers to cognitive dysfunction that persists or arises within 30 days after the procedure, as well as mild or major postoperative neurocognitive disorders (p-NCD) that can be identified up to 12 months after surgery.^10^ To diagnose dNCR and p-NCD, the Diagnostic and Statistical Manual of Mental Disorders, Fifth Edition pillars of diagnosis for neurocognitive disorders^11^ are required: (1) subjective complaint/cognitive symptoms assessed by the patient, a caregiver or a close relative/friend; (2) objective impairment/change assessed by neurocognitive tests and (3) the individual’s functional level related to the activities of daily living.^10^

Previous research demonstrates that approximately 40%–50% of patients undergoing cardiac surgery develop cognitive complications in the early postoperative period.^9^ The aetiology of these complications is believed to be multifactorial, with the proposed mechanisms, including embolisation, neural ischaemia and inflammatory response.^12^ It has been suggested that the use of cardiopulmonary bypass during cardiac surgery also affects cognitive outcomes; however, no definitive conclusions have been reached.^13^ Several risk factors for developing dNCR/p-NCD have been identified, including advanced age, pre-existing cognitive impairment, preoperative depression and frailty, low educational attainment, atherosclerotic cardiovascular diseases, diabetes, prolonged mechanical ventilation and extended surgery duration.^14^,^18^ Currently, routine clinical evaluations of cognitive function are not a part of the preoperative or postoperative assessments. Therefore, knowledge about the range of patient-reported cognitive symptoms and signs that patients may experience, the timing of these events, and their impact on daily life remains limited.

When cognitive function declines, it significantly impacts the patient’s close relatives, resulting in a decreased quality of life and increased caregiver burden.^19^ Close relatives are often the first to notice changes in a patient’s cognitive status.^20^ In this study, the term ‘close relatives’ refers to all individuals identified by the patient as significant to them, which may include close friends and other important figures in their life. These relatives may play a crucial role in diagnosis and support the patient’s recovery process. These aspects have not yet been extensively studied. If patient-reported cognitive symptoms are effectively assessed and managed, it may lead to the improved quality of life for both the patient and their close relatives.

### Aim

The purpose of this study is to investigate the factors that influence neurocognitive function and patient-reported cognitive symptoms among patients aged 65 and older following cardiac surgery, and explore the impact on the overall postoperative recovery. Additionally, the study aims to describe the perspectives of close relatives on the recovery process. The following scientific questions will be addressed in the study.

What is the incidence of dNCR/p-NCD and the occurrence of patient-reported cognitive symptoms in older adults up to 6 months after cardiac surgery?Is there a correlation between preoperative cognitive status and dNCR/p-NCD, and if so, which cognitive function (executive function, attention and memory) is most affected?Is there a correlation between POD and dNCR/p-NCD, and if so, which cognitive function is most affected?Which factors (eg, age, educational level, duration of surgery, perceived self-efficacy, frailty and mental health and depression) affect the risk of suffering from postoperative cognitive decline?Is dNCR/p-NCD associated with increased symptom burden, impaired functional level, fatigue, frailty, deteriorated quality of life and an increased number of unplanned contacts with healthcare services?How do older adults with persistent cognitive symptom burden experience their postoperative recovery and return to daily life?How do close relatives to older adults with persistent cognitive symptom burden perceive the patient’s postoperative cognitive function and recovery, and how does this affect the relative’s own life?

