### Procedure

#### Preoperative data collection

Before surgery, the patient’s baseline data will be collected approximately 14 days in advance, following their informed written consent to participate in the study. We will measure patient-reported cognitive symptoms, self-efficacy, frailty (if it has not been routinely recorded at the hospital site), fatigue, health-related quality of life and collect demographic data. This data collection can take place digitally, at the hospital or through home visits. The process of collecting data will be thoroughly documented.

All questionnaires will be distributed using the Research Electronic Data Capture (REDCap) system. If participants prefer, the data can also be collected using paper-and-pen questionnaires or through phone assessments. Neurocognitive function will be evaluated using the Mindmore-P tool on a digital platform. Each test begins with an introduction, followed by a practice trial and then the actual test trial, which takes approximately 15–20 min to complete. Although Mindmore-P is self-instructive, a trained test leader (such as a research nurse or researcher) will be available by phone or digital platform for distance assessments, or in person at the hospital, to provide support and answer any questions that may arise. Close relatives of the participants will be asked, after providing their consent, to provide demographic information and respond to questionnaires about the patient’s cognitive function and caregiver burden prior to surgery. Table 2 outlines the outcome measures and the time points for assessment.

**Table 2 T2:** Outcome measurements and timepoint for assessment

Outcomes	Instrument	Timepoint of measurement					
		Preop	Postop day 1–7	At discharge	1 month	3 months	6 months
Participant (patient)							
Cognitive symptoms	SwQoR-Cog	X		Every seventh day → → → → → →→→→			X
Neurocognitive function	Mindmore-P	X			X	X	X
Delirium	Nu-DESC		X				
Frailty	CFS	X					X
Fatigue	FSMC	X					X
Self-efficacy	S-GSE	X			X	X	X
Depression	PHQ-9	X			X	X	X
Health-related quality of life	RAND-36	X					X
Functional level	WHODAS 2.0	X			X	X	X
Experience of postop recovery	Interview						X
Unplanned hospital visits	Study specific						X
Demographical data	Study specific	X					
Surgical and postop data	Patient record			X			
Participant (close relative)							
Cognitive assessment for others	CFQ-f	X			X	X	X
Assessment of perceived burden	ZBI-12	X			X	X	X
Experience of postop recovery	Interview						X

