### Data analysis and statistics

Descriptive statistics will be presented, including frequency, percentage, mean, SD or range, as appropriate. We will calculate standardised reliable change Z-scores for each neurocognitive test (n=4) based on the differences in patients' test results from baseline to postoperative assessments, adjusting for variance using Swedish normative data.^45^ In accordance with the guidelines established by Borchers *et al*. in their 2021 review^46^ and Evered *et al*. in their 2018 nomenclature,^10^ we define objective decline in dNCR/p-NCD as mild (1–2 SD) and major (greater than 2 SD) for each test result. This classification requires at least two test results for accuracy.

Parametric and non-parametric tests will be used to identify differences between groups regarding outcomes and demographic characteristics. We will assess potential associations between our dependent variable (neurocognitive performance) and independent variables using multivariate logistic regression analysis. A p value of less than 0.05 will be considered statistically significant in all analyses.

Mixed effect models will be used for the analysis of longitudinal data and potential clustering of data on patient-reported cognitive symptoms. Trajectories of patient-reported cognitive symptoms will be analysed with statistical process control (SPC).^47^ The SPC involves the creation of control charts that are used to evaluate how processes change over time. A pooled SD measure based on the first two trials from SwQoR-Cog will be used for the calculation of control limits. X-bar and S charts will be used for process analysis on group level. Individual processes will be analysed with I-diagrams within SPC.

The SwQoR-Cog and CFQ-f will undergo further psychometric evaluation, guided by the COnsensus-based Standards for the selection of health Measurement INstruments.^48^ Additionally, interviews with patients and their close relatives will be analysed using qualitative content analysis, which is appropriate for exploring and identifying knowledge where evidence is limited.^49^ Finally, we will synthesise both quantitative and qualitative findings to identify similarities and differences, examining whether the qualitative results converge with or diverge from the quantitative findings.^21^

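### Question 2 relates baseline cognition to a decline score that contains that same baseline, so regression to the mean makes better scorers appear to decline more

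*Protocol article*

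**What the plan says.** In the Aim section, question 2 asks "Is there a correlation between preoperative cognitive status and dNCR/p-NCD" and, if so, "which cognitive function (executive function, attention and memory) is most affected".

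Under Preoperative data collection, "Neurocognitive function will be evaluated using the Mindmore-P tool on a digital platform". Table 2 lists no other cognitive performance test before surgery. The other preoperative measures that touch on cognition are the patient's symptom questionnaire (SwQoR-Cog) and the relative's questionnaire (CFQ-f).

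Data analysis and statistics bases reliable-change Z-scores for four tests on the "differences in patients' test results from baseline to postoperative assessments", "adjusting for variance using Swedish normative data". Objective decline is graded "mild (1–2 SD) and major (greater than 2 SD) for each test result", and the section adds: "This classification requires at least two test results for accuracy". Associations with neurocognitive performance are to be tested by logistic regression at p < 0.05.

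The limitations in the Discussion deal with learning effects. They do not deal with the baseline forming part of the outcome.

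**The concern.** A patient who happens to test above their usual level before surgery will tend to score lower at follow-up without any change in ability. One who tests below it, because of illness or stress before surgery, will tend to score higher. A difference score records the first as decline and the second as improvement. Relating that score to the baseline therefore produces an association in a known direction: high scorers look at risk and low scorers look protected. Dividing by a normative SD changes the units of the difference but leaves the baseline error in it.

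The Introduction lists pre-existing cognitive impairment as a risk factor, which is the opposite direction. A true effect of that kind could be hidden or reversed. The artefact also grows as a test's reliability falls, so comparing the strength of the baseline-decline association across domains partly compares the reliabilities of the tests.

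**Working it through.** **Inputs from the article.** Four tests; decline cut at 1 SD; at least two test results required, read here as decline on at least two of the four; alpha 0.05; 220 patients with 15% dropout, so 220 × 0.85 = 187 evaluable. The article gives no figure for the baseline-decline association, so there is none to reproduce. The sample size is not disputed here.

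**Assumptions.** The article gives no reliability coefficient, so the test-retest correlation r is taken as 0.6 to 0.9. Nobody truly changes, variances are equal at both times, and errors are independent across tests unless stated. The true-score correlation between tests is 0.4 for the odds ratios (0.3 to 0.5 for the false-significance rates).

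**One test, continuous change.** With baseline B and follow-up F of unit variance and correlation r, Cov(B, F − B) = r − 1 and Var(F − B) = 2(1 − r). Hence corr(B, F − B) = −√((1 − r)/2). At r = 0.7 this is −√0.15 = −0.39.

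**One test, decline of at least 1 SD of change.** Given B = b, the change has mean −(1 − r)b and variance 1 − r². So P(decline | b) = Φ((−√(2(1 − r)) + (1 − r)b)/√(1 − r²)). At r = 0.7:
- b = +1: Φ((−0.775 + 0.3)/0.714) = Φ(−0.66) = 25.3%
- b = −1: Φ((−0.775 − 0.3)/0.714) = Φ(−1.50) = 6.6%
- ratio: 3.8

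**Two-of-four rule and false significance (simulated).** The last two columns give the percentage of studies with n = 187 in which logistic regression on baseline reaches p < 0.05, against a nominal 5%.

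| r | corr(B, change) | OR per SD of mean baseline, two-of-four | Falsely significant, single test | Falsely significant, two-of-four |
|---|---|---|---|---|
| 0.6 | −0.45 | 1.7 | about 99% | 61–66% |
| 0.7 | −0.39 | 1.6 | 95–96% | 43–55% |
| 0.8 | −0.32 | 1.4 | 81–83% | 29–35% |
| 0.9 | −0.22 | 1.3 | 50–54% | 18–22% |

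At r = 0.7 about 17% of the top baseline tertile and 7% of the bottom tertile are classed as declined.

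**With a real effect.** Let true decline increase by 0.2 SD per SD of lower true baseline. At r = 0.7 the OR per SD of true ability is 0.57, but the OR on observed baseline is 0.91. At r = 0.6 the observed OR is 1.08, so the sign reverses. The distortion shrinks as reliability rises.

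**Checking the remedy, no true change.** The regression-based score is Z = (F − rB)/√(1 − r²).
- Each test against its own baseline: correlation 0.00, OR 1.00.
- Each test conditioned only on its own baseline, then two-of-four against mean baseline: OR about 0.67 to 0.77, so the bias reverses.
- Each test conditioned on all four baselines, then two-of-four against mean baseline: OR 1.00.
- Planned difference score on one test, predicted from the other tests' baselines: OR 1.00 with independent errors, but 1.31 at r = 0.7 when errors within a session correlate at 0.3.

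**The case against.** The strongest reply is that the article fixes neither side of the association. It does not name Mindmore-P as preoperative cognitive status, gives only a generic sentence on logistic regression, and cites outside sources for the reliable-change formula. This stands in part: the identification is an inference. It is nevertheless the natural one, because question 2 names domains that the test battery covers and the alternatives are questionnaires. The difference-based score and the variance-only use of norms are stated choices, not detail left to an analysis plan.

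Second, the Introduction requires complaint and functional criteria as well as objective change for dNCR/p-NCD. This stands. The figures above describe the objective component, and the full diagnosis would show a weaker artefact. It would still show one, because objective change remains a required criterion.

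Third, the size depends on assumed reliabilities. That is correct and is why a range is shown, but the direction holds for any r below 1.

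A reader might also infer that the least reliable test will show the most decline. The calculation does not support this. If change is scaled by its own SD and nobody changes, every test shows about 16% at or beyond 1 SD. With a true drop of 0.3 baseline SD, Φ(−1 + 0.3/√(2(1 − r))) gives 25% at r = 0.6 and 37% at r = 0.9, so the least reliable test shows the least. Only the strength of the baseline-decline association is inflated by low reliability.

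**Conclusion.** The point holds for question 2. Followed as written, with Mindmore-P as preoperative status, the scoring rule produces an association when nobody changes: a correlation of −0.45 to −0.22 for a single test, and an OR of about 1.7 to 1.3 per SD of higher mean baseline under the two-of-four rule, for assumed r of 0.6 to 0.9. These figures also assume equal variances and errors independent across tests, and they apply to the objective component only. The direction opposes the cited risk factor and can mask or reverse it.

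A reader might infer that the planned dNCR incidence, or the sample size built on a 25% rate, fails for the same reason. This argument does not show that. It concerns the link between baseline and change, and a difference-based classification remains reasonable for incidence.

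**What to change.** State that preoperative cognitive status in question 2 means the baseline Mindmore-P result, if that is intended. For question 2 only, replace the difference score with a regression-based change score conditioned on the baseline measure or measures used as predictor:

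- For single-test or domain analyses, condition on that test's own baseline.
- If a composite baseline is related to the two-of-four classification, condition each test's follow-up score on all four baselines.
- Take slopes and residual SDs from stable people (normative or test-retest data). Fitting them in the patients would remove any true association as well. The Mindmore test-retest study cited in the Discussion is the first place to look, but the article does not show whether it reports the coefficients needed.
- If such coefficients are unavailable, predict decline on one test from baseline on the other tests as a sensitivity analysis, and state that this assumes independent errors across tests within a session.
- Do not interpret the unadjusted baseline-versus-decline association as an effect of preoperative status.

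Keep the planned classification for incidence. The cost is analysis wording and code, with no new data. The small downside is a second decline score in the study, which must be labelled as specific to question 2.

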## Methods and analysis

### Study design and setting

A longitudinal observational study using a mixed-method convergent parallel design will be conducted at two thoracic surgical departments in Sweden.^21^ The study will adhere to the STrengthening the Reporting of OBservational studies in Epidemiology guidelines.^22^ Recruitment for the study began in November 2024 at the first site and in March 2025 at the second site.

### Participants

Participants in the study will consist of older adults aged 65 years and above who are undergoing open cardiac surgery (eg, bypass grafting or valve replacement or a combination of both). The goal is to include a total of 220 patients, along with one accompanying close relative for each patient. The sample size estimation is based on a statistical power analysis aimed at detecting a 25% rate of dNCR among participants 1 month after surgery, using a normal SD with α=Zα = 1.960 and factoring in a 15% dropout rate.

#### Inclusion criteria

Scheduled for elective or urgent cardiac surgery.Resident in the area/region for the current thoracic clinic.Able to read and understand Swedish.

#### Exclusion criteria

Participants with physical, mental or cognitive difficulties preventing them from completing the cognitive tests.Individuals who have undergone surgery within the last 6 months.

The close relative will be eligible for inclusion if (1) the relative is 18 years or older and (2) can read and understand Swedish.

### Recruitment

Potential participants (patients) will be assessed for eligibility and provided with both written and verbal information about the study. Following this, they will be asked to participate. If a patient chooses to be included, a close relative will also be invited to participate in the study. If the patient does not have any relatives or their close relatives choose not to participate, they will not be excluded from the study. Close relatives will receive written and verbal information about the study and will, subsequently, be enrolled after providing informed written consent. Recruitment will be conducted by a research nurse at each study site.

